## Abstract

**Background:**

Early neurodevelopmental risks, compounded with traumatic medical experiences, contribute to emotional and behavioral challenges in as many as 1 in 2 children with congenital heart disease (CHD). Parents report a strong need for supports; yet, there remains a lack of accessible, evidence-based behavioral interventions available for children with CHD and their families. I-InTERACT-North is a web-based stepped-care mental health program designed to support family well-being and reduce behavioral concerns through positive parenting for children with early medical complexity. In previous pilot studies, the program was effective in increasing positive parenting skills and decreasing child behavior problems, with high parent-reported acceptability. This paper presents the protocol for the first randomized study of stepped-care parent support for families of children with CHD.

**Objective:**

This study will involve a single-site, 2-arm, single-blind randomized controlled trial to evaluate (1) the feasibility and acceptability of a web-based stepped-care parent support program (I-InTERACT-North) and (2) the effectiveness of the program in enhancing positive parenting skills and reducing behavioral concerns among families of children with CHD.

**Methods:**

Families will be randomized (1:1) to either receive treatment or continue with care as usual for 12 months. Randomization will be stratified by child’s sex assigned at birth and baseline parent-reported child behavior intensity. Primary outcomes include positive parenting skills and child behavior at baseline, 3 months, 6 months, and 12 months. Secondary outcomes include parental mental health, quality of life, service usage, and feasibility including program reach and adherence. A sample size of 244 families will provide >95% power to detect an effect size of *d*=0.64. Based on attrition data from pilot studies, a target of 382 families will be enrolled. Parent reports of acceptability, adoption, and suggested adaptability of the program will be examined using cross-case thematic analyses. Primary efficacy analysis will be conducted using an intent-to-treat approach. Generalized estimating equations will be used to examine changes in positive parenting. Child behavior, quality of life, and parent mental health will be tested with repeated-measures analyses. Additional sensitivity and replication analyses will also be carried out.

**Results:**

Recruitment began in February 2024, and recruitment and follow-up will continue until January 2029. We anticipate results in late 2029.

**Conclusions:**

This study aims to test the effectiveness of I-InTERACT-North web-based stepped-care parent support in improving positive parenting skills and reducing child behavior problems in families of children with CHD compared with a care as usual control group. Results will inform future clinical implementation and expansion of this program among families of children with early medical conditions.

**Trial Registration:**

ClinicalTrials.gov NCT06075251; https://clinicaltrials.gov/study/NCT06075251

**International Registered Report Identifier (IRRID):**

DERR1-10.2196/64216

## Introduction

Congenital heart disease (CHD) is the world’s leading birth defect, impacting 1% of Canadian children [1,2]. Advances in medical care have significantly enhanced the survival rate post CHD diagnosis; however, children with CHD continue to face greater and persistent challenges in learning, behavior, and socioemotional development than their healthy-born peers [3]. Adverse neurodevelopmental outcomes are influenced by evolving genetic, cardiovascular, and psychosocial risk factors in early childhood [4]. These early risks, compounded with the emotional toll of traumatic medical experiences for children and parents (the word “parent” is used here and throughout this paper to denote the primary caregivers; this may include biological parents, adoptive parents, foster parents, grandparents, family members, or other individuals responsible for childcare), can contribute to the emergence of emotional and behavior problems (eg, noncompliance, acting out) in as many as 1 in 2 children with CHD [5-11]. Yet, a gap remains in the availability of accessible, evidence-based treatments to support the social, emotional, and behavioral needs of children and families affected by CHD [12-14].

When considering factors affecting children’s development, parenting and parent-child relationships emerge as potential modifiable determinants of health. Indeed, positive parenting, which includes parental flexibility, responsiveness, constructive parenting, and emotional warmth [15], is a well-established universal protective factor promoting optimal child emotional and behavioral outcomes [16,17]. Several widely used mental health interventions addressing childhood emotional and behavioral problems target positive parenting skills, aiming to strengthen parent-child interactions to improve child behavior [18-20]. Examples include the Incredible Years Parenting Program [21] and the Positive Parenting Program (Triple P [22]). These programs target children identified as at-risk based on socioeconomic factors; however, in recent years, investigators have considered the potential for positive parenting to optimize outcomes among medically at-risk children [23,24]. In our work among children with CHD and their families, parents prioritized mental health support for their children and themselves to empower their parenting skills and confidence. Parents also noted the burdens associated with additional in-person mental health programming, highlighting the need for more accessible web-based services [14].

In response to these identified needs, our team at The Hospital for Sick Children developed the I-InTERACT-North program with and for families of children with CHD by adapting components from the parenting program I-InTERACT (Internet-based Interacting Together Everyday Recovery from Traumatic Brain Injury [25]). I-InTERACT was developed at the Cincinnati Children’s Hospital Medical Centre by Wade and colleagues [25] and uses in vivo coaching to improve positive parenting skills in a telehealth format. The original I-InTERACT program was shown to improve positive parenting skills and child behavior following pediatric traumatic brain injury (TBI [25,26]). While children with CHD share some underlying vulnerabilities with children with TBI, parents of children with CHD have reflected how their prenatal and neonatal experiences were unique from parents of children with TBI within an initial needs assessment [14]. Specifically, parents described stress beginning prior to or at birth, followed by significant fears and uncertainty during their child’s early medical and developmental journey. With this input, the I-InTERACT-North program caters specifically to families of children with congenital and neonatal conditions, including CHD, by providing new information regarding the unique neurodevelopmental and psychosocial impact of these conditions [27]. Likewise, program strategies are tailored to family-specific behavioral concerns, including psychoeducation, coaching, and problem-solving, to address their individual child’s needs in the context of their medical and treatment history. Following an initial pilot, which found I-InTERACT-North to be feasible, acceptable, and effective in increasing positive parenting skills and decreasing child behavior problems [28], our group further adapted the program to a novel stepped-care model, as informed by patient-orientated approaches, in which families can access needs-matched incremental supports (ie, an introduction session, an abbreviated program, and a full program [29]). Pilot data from the stepped-care program has demonstrated high acceptability, with strong parent-reported accessibility and adaptability of care to their family’s needs. Likewise, pilot data demonstrated the program’s success in improving positive parenting skills (*P*<.001; η^2^=0.850) and child behavior problems (*P*=.001; *d*=0.390). Without sacrificing efficacy, stepped-care I-InTERACT-North delivery also improves efficiency and contributes to precision mental health by offering scalable services that are adaptable to the needs of families.

To date, efficacy and feasibility of I-InTERACT-North have not been systematically investigated in children with CHD exclusively using a randomized controlled trial (RCT) design. This study aims to test the effectiveness of I-InTERACT-North in improving positive parenting skills and reducing child behavior problems in families of children with CHD compared with care as usual (CAU). This manuscript provides rationale for and information regarding the stepped-care parent support program and describes how intervention effectiveness will be evaluated in families of children with CHD. This study protocol manuscript was developed and submitted before data collection and analyses were completed.

## Methods

### Study Design

The proposed hybrid type 1 study is a single-site, 2-arm, single-blind RCT designed to simultaneously assess (1) feasibility and acceptability of an RCT of stepped-care web-based parent support (ie, adherence, fidelity, costs, and acceptability) and (2) efficacy of the stepped-care I-InTERACT-North program in improving positive parenting skills and child behavior among families of children with CHD.

Hypothesis 1: based on our pilot data, we hypothesize that the stepped-care program will demonstrate program feasibility (ie, adherence and fidelity, >70%) and high acceptability (ie, based on postintervention program ratings, thematic analysis of feedback, >90%) across CHD families.

Hypothesis 2: we hypothesize that positive parenting skills and child behavior will improve at the end of the treatment among participants in the treatment arm compared to CAU and remain improved compared with CAU at 12 months. We consider positive parenting skills as the primary proximal outcome and child behavior (co–primary outcome) as mediated by improvements in parenting. We also consider secondary outcome changes in parent mental health and family quality of life.

After completion of baseline measures, families will be randomized to receive CAU or active I-InTERACT-North stepped-care treatment. Randomization will be stratified by sex assigned at birth (male, female) and baseline child behavior severity (Eyberg Child Behavior Inventory [ECBI] intensity *t* score above or below cutoff of 60) and executed by a computerized randomization system on REDCap (Research Electronic Data Capture; Vanderbilt University) [30]. Families in both conditions will complete follow-up measures at 3 months, 6 months, and 12 months postbaseline (Figure 1). Families randomized to CAU will receive no direct parent treatment other than clinical care provided in cardiac follow-up (ie, child assessment and consultation), which will be documented accordingly. The CAU families will be offered I-InTERACT-North after completion of their 12-month follow-up measurements. Participants cannot be blinded to their condition, but they will be blinded to primary outcomes and hypotheses. Independent study staff responsible for coding the primary outcomes (ie, positive parenting skills) will be blind to participant allocation, outcomes, and baseline or follow-up status.

**Figure 1 figure1:**
[figure not shown]
Flowchart of planned study recruitment, retention, and procedures. I-InTERACT: Internet-based Interacting Together Everyday Recovery from Traumatic Brain Injury.

### Ethical Considerations

This study was approved by the research ethics board at The Hospital for Sick Children (1000080752). Given that the study participants are parents, all will provide written, informed consent. It is specified that participants can withdraw their consent at any given time in the study upon request. All patient data will be deidentified and stored in secure locations. Families are compensated with a CAD $25 (US $18.47) gift card at each timepoint (ie, baseline, 3 months, 6 months, and 12 months).

### Participants

Participants will be recruited from The Hospital for Sick Children in Toronto, Ontario, which is the largest cardiac care center in Canada. Eligible participants must be parents of a child aged 3-9 years (at time of enrollment) with CHD followed at The Hospital for Sick Children. The family must reside in the province of Ontario given professional jurisdiction pertaining to psychological care provision. Exclusion criteria include significant medical issues requiring inpatient care, current participation in a similar family or parent therapy program (eg, Incredible Years Parenting Program [21] and Positive Parenting Program [Triple P] [22]), or previous participation in I-InTERACT-North pilot studies. There are no exclusions based on medical or mental health diagnosis; however, any patients undergoing significant issues requiring inpatient care will be deferred and reapproached at a more appropriate time. To overcome access inclusion criteria, we will provide families in need with tablets based on our Canadian pilot (5%) and Canadian web-based coverage status. Interpreter services are also available for recruitment, informed consent, and I-InTERACT-North treatment sessions.

### Recruitment

Participants will be recruited through three channels: (1) existing cardiology and neurology research registries at The Hospital for Sick Children (REB #1000051521 and #1000052378) comprising families of children with CHD who have consented to future contact regarding research studies, (2) word-of-mouth recruitment by coinvestigators and collaborators providing clinical care to eligible families, and (3) social media recruitment via Facebook groups moderated by parents for CHD caregivers at The Hospital for Sick Children.

### Intervention

I-InTERACT-North is a stepped-care web-based parenting program consisting of 3 tiered steps of increasing therapeutic intensity (Figure 2). In step 1, participants are matched with a therapist for an introductory appointment to review their concerns and goals for the program. Steps 2 and 3 combine web-based therapy sessions with web-based psychoeducational modules that introduce positive parenting skills (eg, labeled praise, reflective responses; Figure 3) as well as child behavior management strategies. Each web-based module concludes with a brief quiz to assess engagement and understanding. Parents complete the web-based modules asynchronously before their web-based therapy appointment, where they review the strategies and engage in active coaching with their therapist while their child is present. Step 2 includes the first 2 therapy sessions and step 3 consists of an additional 5 sessions. Depending on the number of steps completed, as well as scheduling of sessions, I-InTERACT-North may last anywhere from 1 day (ie, 1 single-hour session) up to 7 weeks (for weekly sessions) or 14 weeks (for biweekly sessions).

A collaborative approach to treatment planning (ie, step-up or step-down as outlined by Kennedy et al [31]) is used with families at the end of steps 1 and 2 to decide whether they will proceed with treatment. Step-up indicators include low positive parenting skills as coded from observed parent-child interactions, high child behavior severity, and high in-session ratings of the family’s “top problems” [31,32].

Each session follows a manualized therapy protocol to optimize therapist fidelity. All sessions are recorded (with written consent from the participant) and reviewed in supervision. Therapy sessions are delivered via Zoom (Zoom Video Communications, Inc) [33]. All I-InTERACT-North therapists possess masters-level (or higher) education in clinical psychology and come from diverse cultural and language backgrounds. All therapists undergo extensive training and ongoing supervision to ensure program fidelity; this includes a 2-day synchronous training course, 3-6 months of case shadowing, and regular individual and group supervision by a licensed psychologist upon commencing independent program delivery.

**Figure 2 figure2:**
[figure not shown]
Stepped-care model of I-InTERACT-North. I-InTERACT: Internet-based Interacting Together Everyday Recovery from Traumatic Brain Injury.

**Figure 3 figure3:**
[figure not shown]
I-InTERACT-North web-based psychoeducational module. I-InTERACT: Internet-based Interacting Together Everyday Recovery from Traumatic Brain Injury.

### Measures

#### Overview

Data collected in this RCT include video recordings of parent-child interactions, medical chart extractions, and parent-report questionnaires. All participant-reported measures are completed via REDCap [30] at baseline, 3 months, 6 months, and 12 months (Table 1).

**Table 1 table1:** Baseline and outcome measures by timepoint.

Measure	Timepoint			
	Baseline	3 Months (± 3 weeks)	6 Months (± 3 weeks)	12 Months (± 3 weeks)
Chart review	✓			
DPICS^a^	✓	✓	✓	✓
ECBI^b^	✓	✓	✓	✓
DASS^c^	✓	✓	✓	✓
EQ-5D-5L	✓	✓	✓	✓
CSRI^d^	✓	✓	✓	✓
Parent Acceptability Questionnaire^e^		✓		

^a^DPICS: Dyadic Parent-Child Interaction Coding System.

^b^ECBI: Eyberg Child Behavior Inventory.

^c^DASS: Depression and Anxiety Stress Scale.

^d^CSRI: Client Services Receipt Inventory.

^e^For families randomized to I-InTERACT-North.

#### Baseline Data

Chart extraction is performed by a research coordinator at baseline. Data collected include the following: CHD type, surgical history, weight and gestational age at birth, current and comorbid medical and mental health diagnoses, presence of pregnancy or delivery complications, seizures, vision problems, hearing problems, motor problems, and cerebral palsy.

For participants with neonatal magnetic resonance imaging data available, maximal total white matter injury (WMI) volume is documented and will be used for exploratory analyses in this study. WMI volume is calculated based on manual segmentation on the pre- and postoperative magnetic resonance imaging. WMI severity at each time point is categorized with a score of 0-3 (0: none; 1: minimal; 2: moderate; and 3: severe [6]).

Parents will also complete a background questionnaire, which includes questions assessing family history, demographic variables (ie, cultural identity, parents’ education, and employment status), and characteristics of the home environment (ie, number of people living in the home, languages spoken in the home).

### Primary Outcomes

Feasibility outcomes include program reach and adherence (ie, proportion of eligible families who enroll and complete the study) and program fidelity (assessed with a therapist checklist completed after every session).

Two primary outcomes are evaluated for the second objective: positive parenting skills and child behavior. Positive parenting skills are evaluated using the Dyadic Parent-Child Interaction Coding System (DPICS [34]). One member of a team of 3 coders, blind to condition, will observe a 5-minute recording of parent-child interactions and count the frequency of specific positive parenting skills (eg, labeled praise, behavioral descriptions, commands, questions, etc). In our team’s previous studies, interrater reliability coefficients were very high (>0.96 [28,29]). Throughout the RCT, 20% of all videos are double coded to prevent coder drift and coders meet regularly for consensus. In the case that reliability falls below α=.80, the team of coders will convene to reestablish consensus. The second primary outcome, child behavior, is measured with the parent-report ECBI [35]. The ECBI consists of 36 items describing various behavior concerns (eg, noncompliance, emotional regulation), each rated in terms of frequency from 1 (Never) to 7 (Always) as well as whether parents perceive it to be a problem for them (Yes/No). The ECBI yields an intensity score based on frequency of concerns and a problem score representing the number of concerns noted to be problems for the parents. Previous studies have demonstrated good convergent validity of the DPICS and the ECBI for assessing the impact of parenting skills on child behavior [34].

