### Sample Size and Power Analysis

Based on the size of the research registries available for recruitment and pilot estimates of consent rate (70%), we anticipate that 382 families will consent to participate in the RCT. Using pilot estimates of adherence rate (86%), we anticipate that 328, 282, and 244 families will complete the 3-month, 6-month, and 12-month follow-up measurements, respectively. Samples of 122 participants in each condition at 12 months postbaseline will provide >95% power to detect an effect size of 0.64, which is a medium to large effect size conservatively based on our pilot data. This sample size also achieves a power of 95% for subgroup analyses with subgroups with a split of 50%, which is consistent with or close to that of our pilot data.

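### Adherence is defined as study completion, which the plan projects at 64%, against a feasibility hypothesis of more than 70%; the result depends on which of the article's meanings is used

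*Protocol article*

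**What the plan says.** Four places in the protocol article bear on this.

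- **Study Design, Hypothesis 1.** The stepped-care program is expected to show "program feasibility (ie, adherence and fidelity, >70" per cent. The same section states the schedule for both arms: "Families in both conditions will complete follow-up measures at 3 months, 6 months, and 12 months postbaseline". Care-as-usual families are offered the program only after their 12-month measurements.
- **Primary Outcomes.** Feasibility outcomes include "program reach and adherence (ie, proportion of eligible families who enroll and complete the study", together with fidelity from a therapist checklist.
- **Sample Size and Power Analysis.** From "pilot estimates of consent rate (70" per cent and the size of the registries, "we anticipate that 382 families will consent to participate in the RCT". Then: "Using pilot estimates of adherence rate (86%), we anticipate that 328, 282, and 244 families will complete the 3-month, 6-month, and 12-month follow-up measurements".
- **Abstract, Methods.** "Secondary outcomes include parental mental health, quality of life, service usage, and feasibility including program reach and adherence".

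**The concern.** Three statements about one quantity do not fit together. The threshold is above 70%. The definition is completion of the study. The projection for completion of the study is below 70%. The word adherence also changes meaning: in the Primary Outcomes section it concerns finishing the study, and in the sample size section it is the share kept from one follow-up to the next.

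Feasibility is the first of the trial's two objectives and has a numeric expectation attached. If the definition is followed, a trial that runs exactly as planned would report its adherence hypothesis as not met. If the meaning is chosen later, the result can be settled after the data are seen.

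There is also a question of what is being measured. Hypothesis 1 is about the program. Study completion is about returning follow-up measures, and half of the randomised families have no program to adhere to during those 12 months. In the treated arm, a family could skip sessions, return every questionnaire and count as adherent; another could finish treatment, miss the 12-month visit and count as non-adherent.

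**Working it through.** **Inputs (all from the article).** Enrolled: 382. Adherence rate: 86%. Projected completers: 328, 282 and 244 at 3, 6 and 12 months. Consent rate: 70% in the pilot (sample size section) and 65% to date (Results). Threshold: above 70% (Hypothesis 1).

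**Step 1. Reproduce the plan's projections.** Compound 86% over the three follow-ups:

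- 382 × 0.86 = 328.5 (stated 328)
- 382 × 0.86² = 282.5 (stated 282)
- 382 × 0.86³ = 243.0 (stated 244)

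All agree within about one family. The 86% is therefore retention per follow-up interval, applied three times.

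**Step 2. Compare each available meaning of adherence with 70%.**

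| Meaning | Calculation | Value | Above 70%? |
|---|---|---|---|
| Retention per follow-up interval | as stated | 86% | yes |
| Enrolled families still in at 3 months | 328/382 | 85.9% | yes |
| Enrolled families still in at 6 months | 282/382 | 73.8% | yes |
| Enrolled families completing the study (12 months) | 244/382 | 63.9% | no |
| Eligible families who enroll and complete | 244/(382/0.70) = 244/546 | 44.7% | no |

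The fourth row splits the definition into its two parts: reach is enrolled over eligible, and adherence is completers over enrolled. It needs no figure beyond the sample size section. The last row takes the definition as a single proportion and assumes that the 70% consent rate has eligible families as its denominator. The article gives no count of eligible families, so this is an assumption. With 65% consent the figure is 244/(382/0.65) = 244/588 = 41.5%.

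**Step 3. How far short is the 12-month figure?** More than 70% of 382 means at least 268 families (0.70 × 382 = 267.4), which is 24 more than the 244 projected. In terms of interval retention, r³ must exceed 0.70, so r must exceed 0.70^(1/3) = 0.888. The plan uses 0.86. At 0.89 the result would be 0.89³ = 70.5%, just above the threshold.

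**Step 4. Whose completion is counted?** The definition starts from eligible families who enroll, which is before randomisation, and both arms are followed to 12 months. With 1:1 allocation, about half the denominator is care as usual.

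**The case against.** **The pilot meaning may be the intended one.** Hypothesis 1 is said to rest on pilot data, and the pilot adherence rate is 86%. On that usage, or at 3 months when most treatment schedules have ended, the criterion is met. This stands as far as it goes: the criterion is not missed on every reading. It does not remove the problem, because the outcome as defined refers to completing the study, and that is projected at 64%.

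**The 45% tests something the plan never set.** The threshold is attached to adherence and fidelity, not to reach, and the number eligible is unknown. This stands. A reader might take 45% as the main result; the documents do not support that, and the point rests on the 64%.

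**The projection is only a planning figure.** This also stands. If 63.9% were the true rate, a binomial calculation gives about a 0.6% chance of exceeding 70%. That treats a pilot-based rate as known, and a gain of three percentage points per interval would reverse the outcome. The supportable statement is that the criterion is expected to be missed, not that it is bound to be.

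**Feasibility is reported descriptively.** The analysis section plans descriptive data on adherence, fidelity and costs, and no stopping or progression rule hangs on the 70%. A reader might infer that the trial could not answer its feasibility question at all. The text does not support that: fidelity, costs and acceptability are unaffected, and the components would still be reported. What remains is a numeric hypothesis with no single meaning.

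**Completion in both arms is relevant to the feasibility of a randomised trial,** which is how the Study Design section frames the first objective. That is a good reason to report retention. It is not a reason to call retention adherence to the program, which is what Hypothesis 1 is about. The article is condensed and a fuller document may define adherence by arm, but the definition it does print conflicts with its own threshold and projection.

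**Conclusion.** The point holds as an inconsistency between a stated definition, a stated threshold and a stated projection. On the more favourable reading of the definition, the plan expects 63.9% against a criterion of more than 70%, a shortfall of about six percentage points or 24 families. Other meanings used or implied in the article give 86% or 74% and would pass, so the conclusion on adherence depends on a choice that is not fixed. The definition also includes care-as-usual families and so does not measure program adherence.

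The 63.9% rests only on the sample size section and on taking study completion as the 12-month follow-up. The 45% rests on the further assumption about the consent denominator and is secondary. The fidelity half of the criterion is not affected.

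The differing status of feasibility (secondary in the abstract, primary in the Primary Outcomes section) is a separate labelling inconsistency that should be corrected at the same time.

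**What to change.** 1. **Reach:** enrolled over eligible, reported on its own without the 70% criterion.
2. **Study retention:** by arm at 3, 6 and 12 months, set against the planned 86%, 74% and 64%, also without the 70% criterion.
3. **Program adherence:** I-InTERACT-North arm only, with all families randomised to that arm as denominator and a pre-specified session-completion numerator. Apply the 70% criterion to this alone. The numerator needs thought because the number of steps is agreed family by family. If it counts sessions within the agreed steps, a family that stops after the introductory session is fully adherent and the threshold is easier to pass. Reporting adherence by step reached would make this visible.
4. **Wording:** use retention, not adherence, for the 86% in the sample size section, and give feasibility the same status in the abstract and in the Primary Outcomes section.

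The cost is small: no added families, visits or questionnaires. Session completion and the agreed step must be recorded consistently for every treated family. The measures table does not list such a record, though sessions are recorded and have a therapist checklist. The numerator should be fixed before outcome data are reviewed; as of September 2024 only 24 families had enrolled.
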